
#### Cognitive function.

Cognition will be measured using the NIH Toolbox Cognition Battery [37]. Multiple forms will be used to minimize practice effects. This battery consists of 7 instruments testing 5 cognitive domains: 1. Dimensional Change Card Sort Test (cognitive flexibility); 2. Flanker Inhibition Test (inhibitory control); 3. Picture Sequence Memory Test (episodic memory); 4. Picture Vocabulary Test (language); 5. Oral Reading Recognition Test (language); 6. Sorting Working Memory Test (working memory); and 7. Pattern Comparison Processing Speed Test (processing speed). The battery takes 20 minutes to complete on a tablet.

#### Near point convergence (NPC).

NPC will be measured based on our established protocol [38–42]. Using the accommodative ruler, a target (14-point letter) will be moved toward the eyes at a rate of 1–2 cm/s. NPC will be recorded when participants report diplopia has occurred, or the tester observes eye misalignment. The assessment will be repeated twice, and the mean NPC value will be used for analyses.

#### Optical coherence tomography/angiography (OCT/A).

Retinal neural structure will be imaged using high-definition spectral domain OCT, which will be acquired using a Zeiss Cirrus 5000 OCT scanner. The OCT variables examined will be macula CSF thickness (an indicator of the gain or loss of neurons or glia in the inner nuclear, ganglion cell and nerve fiber layer), and cup-to-disc ratio (an indicator of neurodegeneration at the optic disc). Retinal vascular structure will be acquired using the OCT angiography (OCT/A) capability of the Cirrus 5000. The primary OCT/A variable examined will be foveal avascular zone (FAZ) area reflecting the size of the central portion of the macula which contains no blood vessels, and which increases in size with loss of capillaries in the surrounding region).

#### Semi-structured Interviews.

The interview will assess participants’ relationship status, relationship quality, sexual agency, and overall sexual experiences, including partnered strangulation. For participants in the strangulation group, we will assess strangulation-related characteristics (onset, frequency, duration, single vs. repetitive, reasons for continued engagement, perceived prevalence among their peers); strangulation method (e.g., both hands, ligature); and responses from being strangled (e.g., visual changes, dizziness, disorientation, loss of consciousness, neck pain, bruising, euphoric sensations, as well as their levels of enjoyment and pleasure. The interview will also include questions related to less common “rough sex” behaviors that may be associated with neurological sequelae (e.g., face/head slapping, smothering, gagging). Participants will be asked about contextual issues relevant to their sexual experiences, which may include arousal, orgasm, intimacy, and/or trust. We will transcribe and code the interview data. The study will explore various dimensions of consent, including the timing and frequency of consent, who initiates consent discussions, and whether the act has ever become uncomfortable despite initial consent. If discomfort has occurred, participants will be asked whether they have discussed these experiences with their partner. Interviews will be audio-recorded and transcribed, with the audio files then deleted. Interview data will be coded and analyzed following a thematic analysis approach consisting of five steps following Nowell et al. [43]

### Ethics and dissemination

The study will be conducted in accordance with the ethical principles outlined in the Declaration of Helsinki, 1996. This research was approved by the Indiana University Institutional Review Board (IRB #27400). Data will be collected using REDCap spreadsheet to organize data and store in a secured database until statistical analysis is conducted. The data will be stored indefinitely for data quality purpose.

### Safety considerations and adverse events

There will be an independent safety monitor who will monitor adverse events data, oversee procedures designed to protect the privacy of participants, and report any adverse event. Data and safety monitoring will occur annually. In the event of an adverse event, the safety monitor will prepare and submit a report to the IRB and will communicate between the team and IRB in any necessary investigation.

### Statistical analyses

#### Baseline group analysis.

To test whether neurological outcomes differ at baseline between the strangulation and control groups, we will use multivariable regression models with each baseline neurological outcome as the dependent variable and group (strangulation vs control) as the primary independent variable. For continuous outcomes (e.g., biomarker concentrations, imaging metrics, cognitive scores, NPC distance, OCT measures), we will use linear regression (or generalized linear models with appropriate functions if distributional assumptions are not met). For binary outcomes (e.g., presence/absence of symptoms or threshold-defined impairment), we will use logistic regression. Models will adjust for prespecified baseline covariates that are clinically relevant and/or imbalanced between groups, including age, BMI, prior concussion history, and baseline mental health symptoms. Because baseline neural health may be influenced by contextual factors, we will additionally consider time since last sexual event, substance use, sleep, and ovarian hormone levels/menstrual cycle phase as covariates when relevant to specific outcomes. For imaging outcomes, scanner-related and acquisition covariates (e.g., motion indices) will be included as standard quality-control adjustments. We will control for multiple comparisons using a false discovery rate (FDR) approach within each modality (biomarkers, imaging, ocular/retinal, cognition, mental health). As a complementary approach that leverages correlation among outcomes, we will conduct multivariate testing within domains (e.g., principal-component-based composite scores) to evaluate whether a domain shows an overall baseline difference by group prior to interpreting individual endpoints. Where appropriate, we also may consider exploratory mediation and explanatory models to help explain baseline group differences. We will use mediation analyses to estimate indirect effects while adjusting for confounders.

#### Acute effects.

To examine the acute neurological effects of sexual strangulation, we will use a series of generalized linear mixed models (GLMMs) (or linear mixed-effects models for normally distributed outcomes) with each neurological variable as the dependent variable and visit type (baseline vs. post-acute) as the primary within-person predictor. Models will include a participant-specific random intercept to account for repeated measures. The primary interest will be the group (strangulation vs. control) × time (baseline vs. post-acute) interaction. Within-group time-effects will also be examined to assess group-specific time trends. Prespecified covariates will consider age, prior concussion history, and mental health diagnosis and/or mental health symptoms, as well as potentially adjusting for time since the most recent sexual event. We will also explore by including menstrual cycle phase and/or ovarian hormone levels as covariates. For neuroimaging outcomes, standard acquisition/quality covariates (e.g., motion indices) will be included. To address multiple comparisons across numerous endpoints, FDR will be applied within modality (biomarkers, imaging, ocular/retinal, cognition/mental health).

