#### Screening and enrollment.

Potential participants will be identified primarily through a campus-wide probability survey focused on sexual health and behavior that is administered during the first two to three years of the study, supplemented by community-based recruitment strategies, including university’s classified sites and social media platforms. Individuals who indicate willingness to be contacted for follow-up research will be randomly stratified (via Randomization function within *R*), with first- and second-year students taking the priority spots to accommodate those who are likely be in school throughout the entirety of 30 months follow-up. Invited participants will complete a prescreening questionnaire to confirm eligibility criteria, including age, sexual strangulation history, and key exclusionary medical or neurological conditions. Eligible individuals will be invited to a virtual consent meeting, during which electronic written consent will be obtained. Following the virtual consent meeting, participants will undergo an additional virtual meeting, and research staff will administer QuickSCID-5 (Quick Structured Clinical Interview for DSM-5 Disorders) to assess current and history of mental health diagnosis. When participants endorse any symptoms related to psychosis and/or schizophrenia, research staff will then conduct a SCID-5 Research Version – Psychotic module B/C to determine the eligibility of participants [32]. During the virtual meeting, research staff will also administer The Alcohol, Smoking and Substance Involvement Screening Test (ASSIST) [33]. When participants meet the inclusion criteria and are free of exclusionary criteria, they will be enrolled in the study and assigned a study-specific ID. Prior to baseline visit, participants are asked to abstain from the following behaviors and caffeine: abstain from sex involving choking and any activities involving pressing or squeezing of the neck (e.g., martial arts chokeholds) 48 hours prior to lab visit, no strenuous exercise (e.g., sports games, cross-fit) 24 hours prior to the visits, no mild to moderate exercise on the day of lab visit, no sexual activities on the day of lab visit, and no caffeine on the day of lab visit.

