#### Cumulative effects.

To determine whether cumulative exposure to sexual strangulation is associated with longitudinal changes in neurological health, we will model repeated neurological outcomes collected every 6 months over 30 months using GLMMs (or linear mixed-effects models for continuous outcomes), a similar model structure to the acute aim. Each model will include a participant-specific random intercept to account for within-person correlation. Time will be modeled as a categorical variable (baseline, 6, 12, 18, 24, 30 months) for primary analyses to allow non-linear trajectories, and as a continuous variable in sensitivity analyses.

Primary longitudinal analysis will focus on: (1) overall group differences in trajectories between the strangulation and control groups via group × time interaction, and (2) within-group change over time (especially within the strangulation group) to identify when divergence from baseline emerges. Covariates will include age, prior concussion history, mental health diagnosis, and other clinically relevant time-varying factors assessed at each visit (e.g., mental health symptoms, substance use). For imaging outcomes, motion indices will be included.

To directly test the exposure-response hypotheses, we will incorporate time-varying measures of sexual strangulation exposure (e.g., frequency since last visit and cumulative frequency across follow-up; and, where available, intensity/duration and presence of alteration in consciousness) as predictors of neurological outcomes within the strangulation group. These models will estimate whether higher exposure is associated with worse neurological outcomes and whether this association strengthens over time by including exposure × time terms when appropriate.

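### The primary acute contrast is not adjusted for recent alcohol or drug use, or for other rough-sex acts at the index event, although the protocol treats both as relevant elsewhere

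*Protocol article*

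**What the plan says.** The protocol article gives each of its three quantitative models its own covariate list.

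- **Baseline group analysis.** Beyond the core covariates, "we will additionally consider time since last sexual event, substance use, sleep, and ovarian hormone levels/menstrual cycle phase" are candidates where relevant to the outcome.
- **Acute effects.** "The primary interest will be the group (strangulation vs. control) × time (baseline vs. post-acute) interaction". "Prespecified covariates will consider age, prior concussion history, and mental health diagnosis and/or mental health symptoms", with the further option of "potentially adjusting for time since the most recent sexual event". Then: "We will also explore by including menstrual cycle phase and/or ovarian hormone levels as covariates". Motion indices are added for imaging. A participant random intercept handles the repeated measures.
- **Cumulative effects.** Covariates include "other clinically relevant time-varying factors assessed at each visit (e.g., mental health symptoms, substance use").

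The Semi-structured Interviews section under Measurements covers "less common “rough sex” behaviors that may be associated with neurological sequelae (e.g., face/head slapping, smothering, gagging"). No statistical model uses these acts. The acute interview takes place within 72 hours of the acute visit. Controls have their acute visit after any sexual event without strangulation, and no matching on other features of the event is described. The pre-visit requests, introduced for the baseline visit, end with "no sexual activities on the day of lab visit, and no caffeine on the day of lab visit". They do not mention alcohol or drugs.

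**The concern.** The acute aim compares a planned baseline visit with a visit about 24 hours after a naturally occurring event. What else happened around that event matters more here than in the other two aims. Events with and without strangulation may differ in drinking, drug use or other rough acts.

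The control group removes only what the two kinds of event share. What differs between them is read as an acute effect of strangulation on biomarkers, cognition, convergence and mood. Hypothesis 2b rests on that reading. The protocol treats substance use as worth adjusting for in its other two models, and regards the rough acts as possible neurological causes in their own right. Leaving both out of this model is therefore an inconsistency in the stated plan, and it allows avoidable confounding.

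**Working it through.** **1. The plan's own figure.** The Sample size section gives 60 females per group, d = 0.60 and alpha 0.01 for 80% power. Taking d in SD of change, the standardised contrast is 0.60 / √(2/60) = 0.60 / 0.1826 = 3.286. Two-sided power is Φ(3.286 − 2.576) = 76.1%; one-sided it is Φ(3.286 − 2.326) = 83.1%. The article gives neither sidedness nor the baseline-to-acute correlation, so the 80% cannot be settled. Nothing below depends on it. The 0.60 serves only as a yardstick.

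**2. What the listed covariates can remove.** Write the linear acute model for person i at visit t (0 = baseline, 1 = acute) as

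Y = a + b₁·G + b₂·t + b₃·G·t + c·X + g·U + person effect + error,

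where G is group, X is fixed within a person, and U is a co-exposure that can change between visits. Subtracting baseline from acute gives

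ΔY = b₂ + b₃·G + g·ΔU + error.

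The person effect and X drop out. Age, concussion history and diagnosis are essentially constant over this interval, so as main effects they do not adjust b₃. A stable group difference in habitual drinking also cancels. If U is left out, the expected estimate is b₃ + g × (group difference in mean ΔU).

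**3. The listed terms that can vary.** These are mental health symptoms, time since the last sexual event, cycle phase or hormones, and motion. None measures alcohol, drugs, slapping, smothering or gagging. Symptoms are also among the primary outcomes in Table 1.

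**4. Illustrative size.** The documents give no prevalence and no 24-hour effect for any co-exposure, so both inputs are assumptions. The gap is the group difference in the share exposed at the index event, net of any such difference before baseline. Bias = gap × effect. Rejection is two-sided at 0.01 with 60 per group and no true strangulation effect: Φ(bias/0.1826 − 2.576) + Φ(−bias/0.1826 − 2.576).

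| Gap | Effect (SD of change) | Bias (SD) | Share of 0.60 | Rejection |
|---|---|---|---|---|
| 0.1 | 0.2 | 0.02 | 3% | 0.0104 |
| 0.2 | 0.5 | 0.10 | 17% | 0.0222 |
| 0.3 | 0.5 | 0.15 | 25% | 0.0400 |
| 0.4 | 0.5 | 0.20 | 33% | 0.0695 |
| 0.4 | 0.8 | 0.32 | 53% | 0.2052 |

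**5. Simulation of the middle case.** There were 4,000 runs with exposure in 50% versus 20% of index events, an effect of 0.5 SD and no strangulation effect. With a baseline-type covariate only, the mean estimate was 0.153 SD and rejection 0.0335. With the event-level factor added, these were 0.003 SD and 0.0085. The spread of the estimate grew by about 3%.

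**The case against.** The strongest reply has five parts.

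- **Brevity.** The statistical analysis plan is not shown, and the covariate wording does not read as a closed list. This would answer a complaint about missing detail. It does not explain why an article that gives a separate list per model names substance use twice and leaves it out of the acute model.
- **Exploratory Aim 6.** It will examine sleep and substance, tobacco and alcohol use as contributors to individual responses to sex with and without strangulation. This stands as mitigation, and the authors have clearly not overlooked context. But the aim is exploratory, does not adjust the primary contrast and does not name rough-sex acts.
- **Data may already be collected.** The testing-day questionnaire is described by two examples only, and substance use is said to be assessed at follow-up visits. A reader might infer that event-night drinking goes unrecorded; the documents do not show that. Participants may also be withdrawn for intoxication at a visit, though this does not cover the night before.
- **Causality.** The Discussion already says that the observational design precludes causal inference. A reader might infer that the plan claims causal proof, or that its acute result is bound to be biased toward harm. Neither is supported. The concession is general, however, and does not replace adjustment for a confounder that can be measured.
- **Sleep.** Adjusting every acute model for sleep is tempting, since the baseline model considers it. But Table 1 lists sleep among the primary outcomes, and sleep after the event may be part of the effect. This objection stands in full.

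**Conclusion.** The concern holds in a limited form. As written, the primary acute contrast would keep any index-event difference between groups in substance use or rough-sex acts, and no listed covariate measures either.

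The size and direction are unknown. Over the assumed range the bias is 0.02 to 0.32 SD, or 3% to 53% of the planning effect. It is zero if the groups' events are alike in these respects. For a factor that worsens the outcome, it runs the other way if controls' events involve more of it. Large gaps are less plausible for the rough acts, which the protocol calls less common. The argument that person-constant terms drop out is exact for the linear model with both visits observed, and approximate otherwise. The point merits a change because the remedy is cheap and recall of the event fades.

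**What to change.** 1. Make sure that recent alcohol, cannabis and other drug use is recorded at both the baseline and the acute visit, through the testing-day questionnaire. Name it in the Acute effects section as a visit-level, time-varying covariate.
2. Prespecify a sensitivity analysis of the group × time contrast that adjusts for, or excludes, index events with face or head slapping, smothering or gagging. Ask about these acts in both groups at the post-acute interview.
3. Use sleep only in a sensitivity analysis, and report the estimate with and without it.

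The cost is a few questionnaire items, a slightly larger standard error (about 3% in the simulated case) and a smaller sample in the exclusion analysis.

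### Age, concussion history and diagnosis are listed as covariates with no covariate × time term, so they do not adjust the group × time contrast that is primary for Aims 2 and 3

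*Protocol article*

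**What the plan says.** Under Acute effects the article plans mixed models: "we will use a series of generalized linear mixed models (GLMMs) (or linear mixed-effects models for normally distributed outcomes". The random part is one intercept per person: "Models will include a participant-specific random intercept to account for repeated measures". The contrast is explicit: "The primary interest will be the group (strangulation vs. control) × time (baseline vs. post-acute) interaction".

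The adjustment set follows: "Prespecified covariates will consider age, prior concussion history, and mental health diagnosis and/or mental health symptoms". A further adjustment, for the interval since the last sexual event, is left open. For imaging it adds: "For neuroimaging outcomes, standard acquisition/quality covariates (e.g., motion indices) will be included".

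Under Cumulative effects the structure is described as similar, with six categorical visits. The first primary target is "overall group differences in trajectories between the strangulation and control groups via group × time interaction", and the adjustment set is: "Covariates will include age, prior concussion history, mental health diagnosis, and other clinically relevant time-varying factors assessed at each visit".

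The interactions written out in these two sections are group × time and, for the exposure-response models, exposure × time. No covariate × time term is named. Neither section says in words that covariates enter as main effects only.

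The Participants section admits people with depression, anxiety, bipolar disorder and ADHD, and undertakes to handle these conditions in the analysis.

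**The concern.** Exposure is self-selected, so the covariates are there to deal with differences between the groups that existed beforehand. A random-intercept model with a group × time contrast already removes any fixed difference in level. What it does not remove is a difference in change: if women with a given diagnosis or concussion history change differently over the visits, and that factor is more common in one group, the excess change appears as group × time. A main effect of the factor describes level only and cannot absorb it.

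The article would then report acute and longitudinal contrasts described as adjusted for age, concussion history and diagnosis when, for change, they are not. The undertaking to handle psychiatric conditions analytically would not be met for the primary contrasts of Aims 2 and 3.

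**Working it through.** **Figure to reproduce.** The article gives no number for this adjustment. Its power figures do not bear on the point. The longitudinal planning effect, d = 0.50 (Sample size), serves only as a yardstick.

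**Step 1: algebra.** For participant *i* at visit *t*, with fixed covariate *x* and random intercept *u*, the model as written is

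Y(i,t) = a + b·G(i) + c(t) + d(t)·G(i) + e·x(i) + u(i) + error.

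Her change from baseline is

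Y(i,t) − Y(i,0) = [c(t) − c(0)] + [d(t) − d(0)]·G(i) + error difference.

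Both e·x(i) and u(i) have gone. With complete visits the group × time estimate is the difference between groups in mean change, with or without *x*. If *x* truly adds k to the change of those who have it, and its prevalence differs between groups by Δ, then

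bias in group × time = Δ × k.

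**Step 2: simulation.** All parameters are assumptions, because the documents supply none. A binary confounder has prevalence 50% versus 20% and adds 0.8 to level and 0.5 to change. A standardised age covariate is also included. The true group × time effect is 0, so Step 1 predicts a bias of 0.30 × 0.5 = 0.15. There were 150 datasets per row, with 60 per group for two visits and 100 per group for six. Mean group × time estimates (first follow-up visit against baseline):

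| Setting (linear mixed model) | No covariates | Main effects | Covariate × time |
|---|---|---|---|
| Two visits, complete | 0.161 | 0.161 | 0.022 |
| Two visits, 20% missing at random | 0.163 | 0.165 | 0.023 |
| Two visits, missingness depends on confounder | 0.108 | 0.133 | 0.027 |
| Six visits, missingness depends on confounder | 0.134 | 0.143 | 0.004 |

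In the complete-data row the first two estimates differed by at most 4 × 10⁻¹⁵ in any dataset. The Monte Carlo standard error there is 0.181/√150 = 0.015, so 0.161 agrees with the predicted 0.15 and 0.022 is compatible with 0. With missing visits the main effect does move the estimate, but not towards 0.

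A logit mixed model was fitted to one large dataset. It gave 0.150 without the covariate, 0.158 with its main effect and −0.091 with covariate × time. A single dataset shows only that the main effect hardly moves the estimate. It does not measure bias.

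**Step 3: plausible size.** Assumed ranges are Δ = 0.10 to 0.25 and k = 0.3 to 0.5 SD.

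- Low end: 0.10 × 0.3 = 0.03 SD.
- High end: 0.25 × 0.5 = 0.125 SD, which is 0.125/0.50 = 25% of the longitudinal planning effect.

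**Step 4: false-positive rate.** Take 80 per group (100 less the 20% allowed for dropout or switching) and assume a change SD of 1. Then SE = √(2/80) = 0.158. With shift δ = bias/SE, the two-sided rate is Φ(−z + δ) + Φ(−z − δ).

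| Bias (SD) | δ | Nominal 5% | Nominal 1% (planning alpha) |
|---|---|---|---|
| 0.03 | 0.19 | 5.4% | 1.1% |
| 0.125 | 0.79 | 12.4% | 3.7% |

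At 60 per group, the acute planning size, SE = √(2/60) = 0.183, δ = 0.68 at the high end, and the rate is 3.0% at nominal 1%.

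**The case against.** **Main-effect entry is inferred.** The article never says main effects only, and the full analysis plan, not shown, may specify the interactions. This stands as a limit on certainty. But the article does state the model, the random effect, the contrast, the covariates and the interactions it wants, and following that text gives the result above.

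**The adjustment set is wider than three fixed factors.** A reader might infer that the whole planned adjustment leaves the primary estimates unadjusted. The documents do not support that. Mental health symptoms, substance use, motion indices and possibly time since the last sexual event can vary by visit and do not cancel. Symptoms are a doubtful stand-in for diagnosis, though, because Table 1 makes them primary outcomes that the hypotheses expect to respond to exposure. Main effects of the fixed factors also still do useful work in the baseline regressions and in between-person exposure-response comparisons.

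**Exact cancellation needs complete visits and a linear model.** The plan allows generalised models, missed acute visits, dropout, and truncation of primary data when behaviour changes. This is correct, but those departures loosen the cancellation without removing the bias.

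**The design closes part of the gap.** Controls are age-matched, and head or neck injury in the past six months is excluded. The acute visit is timed to an event after baseline, and nothing in the article suggests age-related change over that interval. What remains most plausible is diagnosis and older concussion history.

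**The planned inference is cautious.** The Discussion says that the observational design does not allow causal conclusions. That tempers interpretation, but does not make an adjusted label accurate.

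**Conclusion.** The point holds for the three fixed covariates and for confounding of change. As written, age, prior concussion history and baseline diagnosis provide no useful adjustment of group × time in either Aim 2 or Aim 3. That is exact for linear models with complete visits and approximately so otherwise. A fixed factor that differs between groups but affects only level does no harm to this contrast. Bias needs both imbalance and an effect on change.

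The size cannot be read from the documents. The 0.03–0.125 SD range, and the false-positive rates that follow from it, rest on assumed imbalances, assumed effects on change and a change SD of 1. The low end is close to harmless; the upper figures are the worst corner of the assumed range and not an expectation. The change is worth making because it is cheap and makes the adjustment do what the article says it is for.

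**What to change.** In Acute effects and Cumulative effects, state that age at baseline, prior concussion history and baseline mental health diagnosis enter with covariate × visit terms, and that group × time is read from that model. In the primary Aim 3 model use categorical visit for these terms, to match its categorical time. Keep linear covariate × time terms for the continuous-time sensitivity analysis; in the primary model they would leave non-linear confounding in place. For Aim 2 linear outcomes with complete pairs, regressing change on group plus the three covariates is equivalent. Restrict these terms to factors fixed before follow-up.

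Cost: with one term per factor, 3 × 1 = 3 extra parameters in Aim 2 and 3 × 5 = 15 in Aim 3, more if diagnosis is coded in several categories. The standard error rises slightly: in one simulated two-visit dataset with 60 per group it went from 0.175 to 0.178. Nothing changes in recruitment or data collection.
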